### Confidentiality {27}

All data are anonymised at source. A log of contacts with participants including address and other contact details will be kept separate from all the research data. Details necessary to contact participants, and for communication with teams will be stored securely in a locked filing cabinet. A numerical system will be used for computerised information so that individual participants will not be identifiable. Participant consent forms will be retained, kept confidential and stored securely. All identifiable data will be destroyed following a period of 7 years (as determined by relevant information governance policies) after the completion of the trial.

Assessment and therapy sessions will be recorded, with consent, using password-protected smartphone or equivalent devices and data will be transferred to secure central storage as soon as possible. When not in use, devices will be stored in a locked cabinet within a locked office.

### Plans for collection, laboratory evaluation and storage of biological specimens for genetic or molecular analysis in this trial/future use {33}

See above {26b}, there will be no biological specimens collected.

## Statistical methods

### Statistical methods for primary and secondary outcomes {20a}

We will report all participant flow in the study in accordance with the CONSORT principles, with the 2018 extension for reporting social and psychological intervention trials ((CONSORT SPI) [31]). Descriptive statistics will be used to summarise assessments of recruitment, drop-out and completeness of therapy.

The primary outcome of voice-related distress as measured by PSYRATS-AH distress dimension score will be analysed using a mixed effects model including data from all time points. Fixed effects will be site, characterisation, baseline assessment for the outcome under investigation, random allocation, time and time*random allocation interactions. Participant and therapist will be included as random intercepts, with the participants in the TAU arm considered as being in individual clusters of size 1. Marginal treatment effects for each pairwise comparison will be estimated for outcomes at each time point and reported separately as mean adjusted differences in scores between the respective randomised groups with 96.5% confidence intervals and two-sided *p* values (to account for correlated multiple comparisons). For continuous secondary outcomes, the same approach will be followed, and for binary secondary outcomes, logistic mixed models will be used.

The random effect structure will account for repeated measures and clustering due to the partially nested design and allow estimates of separate ICCs in both randomised arms.

Cohen’s d effect sizes at 16 and 28 weeks will be calculated as the adjusted mean difference divided by the sample standard deviation of the outcome at baseline and displayed in a forest plot.

### Interim analyses {21b}

There are no planned interim analyses.

### Methods for additional analyses (e.g. subgroup analyses) {20b}

Causal mediation analysis will be based on parametric regression models [50]. For each mediator separately, this involves estimating a linear model for each mediator with random allocation, baseline outcome, baseline mediator, site and characterisation as covariates, and separately estimating a linear model for each outcome with the mediator, random allocation, baseline outcome, baseline mediator, site and characterisation as covariates. The effect of random allocation on the mediator is multiplied by the effect of mediator on the outcome to estimate the indirect effect, and the effect of random allocation on outcome in the model including mediator is an estimate of the direct effect. The indirect and direct effects sum to the total effect and bootstrapping with 1000 replications will be used to obtain valid standard errors for the causal effects.

For the moderation analyses, these will be conducted by adding interaction terms between random allocation, time and the respective moderators. The difference in treatment effect between unit levels of the moderator can be interpreted as the difference in the estimated treatment effect between a participant with a moderator value at baseline of a+ 1 and a participant with a moderator value at baseline of a.

For analyses involving ESM variables as outcome, an additional level of nesting will be included, with multiple ESM observations (level 1) being nested within time points (level 2) and time points as nested within subjects (level 3).

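### The mediation regressions leave out the therapist clustering that the primary model recognises, which can bias the indirect effect and understate its uncertainty if therapists differ materially

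*Protocol article*

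**What the plan says.** For the primary outcome, the protocol article ({20a}) states: "Participant and therapist will be included as random intercepts, with the participants in the TAU arm considered as being in individual clusters of size 1". It adds that the random-effect structure will account for "clustering due to the partially nested design and allow estimates of separate ICCs in both randomised arms". Continuous secondary outcomes follow the same approach.

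Mediation has its own specification in {20b}. The mediator model is described as "estimating a linear model for each mediator with random allocation, baseline outcome, baseline mediator, site and characterisation as covariates". The outcome model is described as "separately estimating a linear model for each outcome with the mediator, random allocation, baseline outcome, baseline mediator, site and characterisation as covariates". The two are combined as a product: "The effect of random allocation on the mediator is multiplied by the effect of mediator on the outcome to estimate the indirect effect". For inference, "bootstrapping with 1000 replications will be used to obtain valid standard errors for the causal effects". Therapist appears in neither list and the resampling unit is not named.

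The only clustering mentioned in {20b} is this: "For analyses involving ESM variables as outcome, an additional level of nesting will be included". The levels it then gives are observations, time points and subjects, without therapist.

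The analyses serve hypotheses 3 (beliefs about voices, AVATAR-extended) and 4 (ESM anxiety, both therapies). The Abstract classes them as secondary.

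**The concern.** Therapist is assigned after randomisation, so randomisation does not protect the path from mediator to outcome against it, and no baseline measure of the participant carries it. Suppose some therapists lower omnipotence beliefs more than others, and the same therapists also lower distress by a route other than those beliefs, such as general skill or alliance. Participants of the same therapist then share a shift in both variables. A regression of distress on the mediator without therapist reads that shared shift as an effect of the mediator. The product of coefficients inherits the error, and a bootstrap reproduces the bias instead of removing it.

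There is a second, simpler effect. Participants of one therapist are correlated on the mediator, so resampling individuals understates the uncertainty of the allocation-to-mediator effect, and hence of the indirect effect.

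At stake are the mechanism claims: whether beliefs or anxiety carry the effect of therapy.

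**Working it through.** **The plan's own figure.** The article gives no sizing for mediation. Its only reproducible figure is the primary sample size: n per group = 2(z₀.₉₈₂₅ + z₀.₉₀)²/0.5² = 8 × (2.108 + 1.282)² ≈ 91.9, so 92 per group and 276 in total; 276/0.8 = 345. This agrees with the article, and 92 per arm is used below.

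**Inputs.**
- From the article: three arms of 92; four sites, with site a covariate; about 20 trained clinicians including a core of 8 ({11a}); standardised effect 0.5, used here for the effect of allocation on the mediator.
- Assumed, because the article gives neither: the therapist ICC (equal for mediator and distress) and the correlation rho between a therapist's effect on the mediator and their direct effect on distress. Therapists are nested in sites and treat both therapy arms. The true mediator effect on distress is zero.

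**Step 1: size of the spurious slope.** Take unit variances and k therapists per site. Two thirds of participants have a therapist. The allocation terms absorb the overall therapist mean. Site is shared with TAU, so it absorbs only part of the differences between sites: it leaves 1/3 of a site deviation in the therapy arms and −2/3 in TAU, and (2/3)(1/9) + (1/3)(4/9) = 2/9. Hence

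spurious slope ≈ rho × ICC × [(2/3)(1 − 1/k) + (2/9)(3/4)/k].

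- 20 therapists (k = 5): bracket = 0.533 + 0.033 = 0.567. At ICC 0.10 and rho 1 the slope is 0.057. Simulation gives 0.057.
- 8 therapists (k = 2): bracket = 0.333 + 0.083 = 0.417. At ICC 0.10 and rho 1 the slope is 0.042. Simulation gives 0.040.
- rho 0: zero by formula and by simulation.

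At ICC 0.10, rho 1 and 20 therapists, the spurious indirect effect is 0.5 × 0.057 ≈ 0.028 SD.

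**Step 2: false-positive rates for the models as listed** (simulation, site adjusted, nominal 5%). For the slope test with rho 0.5 to 0.8 and 8 to 20 therapists:

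| Assumed ICC | Rejection of a true null |
|---|---|
| 0.02 | about 5-6% |
| 0.05 | about 4-7% |
| 0.10 | about 8-14% |

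For the indirect effect with a person-level bootstrap:

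| ICC, rho | 20 therapists | 8 therapists |
|---|---|---|
| no therapist effect | 5% | 3% |
| 0.02, 1 | 4% | 4.5% |
| 0.05, 1 | 6.5% | 6% |
| 0.10, 0.5 | 8% | 5.5% |
| 0.10, 1 | 14.5% | 11.5% |
| 0.20, 1 | 36% | 26% |

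**Step 3: allocation-to-mediator standard error.** Ignoring clustering, the variance of an arm difference is 2/92 = 0.0217. With J therapists it is [(1 − ICC)/92 + ICC/J] + 1/92. At ICC 0.10 and J = 8 this is 0.0098 + 0.0125 + 0.0109 = 0.0332. The ratio of standard errors is √(0.0217/0.0332) = 0.81, an understatement of about 19%. Simulation agrees, at up to about 20%. At J = 20 the variance is 0.0098 + 0.0050 + 0.0109 = 0.0257 and the understatement is about 8%.

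**Step 4: what removes the bias** (20 therapists, rho 1; false-positive rate of the indirect effect).

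| ICC | As listed | Random intercept only | Therapist fixed effects |
|---|---|---|---|
| 0.05 | 6.5% | 5.7% | 4.3% |
| 0.10 | 14.5% | 6.9% | 4.3% |
| 0.20 | 36% | 10% | 4% |

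At ICC 0.10 the spurious slope goes from 0.057 to 0.031 with the random intercept and to 0.000 with fixed effects. Adding the therapist mean of the mediator, set to zero for TAU, likewise restores slope rejection to about 4-6%.

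**The case against.** The strongest reply is that this is a condensed article describing a secondary analysis, and that the statistical analysis plan, not shown here, may add the clustering. The text lists covariates, which need not exclude random effects; {20a} also lists its fixed effects first and its random intercepts afterwards. That has some force. But {20b} does more than stay silent. It gives mediation its own models, lists their terms, mentions extra nesting only for ESM outcomes, and asserts valid standard errors. As it stands, it does not match {20a}.

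Three stronger readings are tempting, and the document supports none of them.

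- A reader might infer that any therapist who improves both beliefs and distress is wrongly counted as mediation. A therapist who lowers distress by lowering beliefs is genuine mediation. Bias needs a correlated effect on distress outside the mediator.
- A reader might infer that false mediation findings are likely. The article gives no ICC and no correlation. Inflation is negligible at 0.02, small at 0.05, and site absorbs part of it.
- A reader might infer that restoring the primary model's random intercept cures the problem. With 20 therapists it removes only about a third to two thirds of the bias. The rest is confounding of mediator and outcome by therapist, and it needs the within-therapist slope.

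**Conclusion.** The point holds in a limited form. The mediation models in {20b} omit the therapist clustering that {20a} recognises, and the claim of valid standard errors is not supported while the resampling unit is unstated. The direction of the bias is away from zero, provided that therapist effects on the mediator and direct therapist effects on distress go together.

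The size rests on assumed values: practically none at a therapist ICC of 0.02, at most a couple of percentage points at 0.05 with correlation 0.5 to 0.8, and roughly 8-14% against a nominal 5% at 0.10. The understated standard error for the allocation-to-mediator effect needs only that therapists vary on the mediator. It reaches about 20% with 8 therapists at ICC 0.10.

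Only hypotheses 3 and 4 are affected; the primary efficacy comparison already includes therapist. The change is cheap and worth making, because the trial means to draw conclusions about mechanism.

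**What to change.** Amend {20b}, or state in the analysis plan that it supersedes {20b}, as follows.

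1. Include a therapist random intercept in both mediation regressions, as in {20a}.
2. In the outcome regression, add the arm-centred therapist mean of the mediator for the therapy arms, set to zero for TAU, or use therapist fixed effects. Take the within-therapist slope for the indirect effect.
3. In the bootstrap, resample therapists as clusters in the therapy arms, each with all of their participants, and resample individuals in TAU.

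The handling of TAU in item 2 must be written out. If each TAU participant is treated as their own cluster when the mean is formed, that mean equals the participant's own mediator value and TAU adds nothing to the slope. In simulation the standard error then rises from 0.061 to 0.077-0.081, about 26-33%. With TAU set to zero it widens by 0-5%.

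Cost: a few sentences and one derived covariate, since therapist identity is already needed for {20a}. Where therapists do vary, the interval for the indirect effect will be wider, which reflects the real uncertainty. If most cases fall to the 8 core therapists, a cluster bootstrap rests on few units, and the report should say so.

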The lack of a treatment as usual (TAU) arm in this study made the absence of difference between the two active treatment groups at 24 weeks hard to interpret. Similarly, attempts to understand the mechanisms of action for AVATAR therapy are more challenging in the context of an active treatment control. With respect to possible factors which may influence treatment response, a recent analysis of in-session ratings (collected only in the AVATAR therapy arm) explored self-reported anxiety and the sense of voice presence (i.e. the extent to which speaking to the avatar was experienced as like talking to the everyday voice). Whilst sense of voice presence remained consistently high across all sessions, there was a significant reduction in anxiety which was driven by a rapid change during sessions 1–3 (phase 1). Notably, improvements in voice frequency and overall severity at follow-up were predicted by an interaction between overall anxiety reduction and sense of voice presence [17]. Allied to clinical reports of significant early improvements [14], this raises the question as to whether a consistent phase 1 focus on exposure and assertiveness to a valid representation of the voice might be sufficient for some individuals; for example, where distress is closely linked to fear, anxiety and relational submissiveness. There would be fewer barriers to training and dissemination of a standardised phase one-based AVATAR therapy compared to the extended therapy, potentially facilitating implementation both across the UK and in other settings worldwide where therapists trained in formulation-based psychological therapies are in short supply.

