#### Hypotheses

AVATAR-brief will be more effective in reducing voice-related distress, total voice severity and voice frequency than TAU at post-treatment (16 weeks) and follow up (28 weeks)AVATAR-extended will be more effective in reducing voice-related distress, total voice severity and voice frequency than TAU, at post-treatment (16 weeks) and follow-up (28 weeks)AVATAR-extended will reduce perceived omnipotence and malevolence (BAVQ-R) compared to TAU and these improvements will mediate change in the primary outcome.In both AVATAR-brief and AVATAR-extended treatment effects on the primary outcome will be mediated by anxiety reduction, as measured by Experience Sampling Methodology (ESM) in daily life.Greater baseline complexity of voice characterisation will moderate the treatment effects of AVATAR-brief and AVATAR-extended compared to TAU. Other clinical characteristics will be explored as potential moderators.AVATAR-brief and AVATAR-extended will both have favourable incremental cost-effectiveness ratios compared to routine care.

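### The mediation model applies one mediator-outcome slope to every arm, although the mediation hypotheses are stated by arm; if slopes differ, the indirect effects are biased in either direction

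*Protocol article*

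**What the plan says.** The section on additional analyses {20b} sets out two linear models for each mediator. The first regresses the mediator on allocation and baseline covariates. The second is described as "separately estimating a linear model for each outcome with the mediator, random allocation, baseline outcome, baseline mediator, site and characterisation as covariates". These are main effects only. The indirect effect is a product of coefficients: "The effect of random allocation on the mediator is multiplied by the effect of mediator on the outcome to estimate the indirect effect". The section adds: "The indirect and direct effects sum to the total effect and bootstrapping with 1000 replications will be used to obtain valid standard errors". Interaction terms with allocation appear only in the next paragraph, for the moderation analyses.

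The Hypotheses section words the mediation claims by arm. For beliefs: "AVATAR-extended will reduce perceived omnipotence and malevolence (BAVQ-R) compared to TAU and these improvements will mediate change in the primary outcome". For anxiety: "In both AVATAR-brief and AVATAR-extended treatment effects on the primary outcome will be mediated by anxiety reduction".

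The background section {6a} reports from the earlier trial that "improvements in voice frequency and overall severity at follow-up were predicted by an interaction between overall anxiety reduction and sense of voice presence". On the source of those data it says: "a recent analysis of in-session ratings (collected only in the AVATAR therapy arm) explored self-reported anxiety and the sense of voice presence".

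**The concern.** Under the written model, the indirect effects of Brief and Extended can differ only through their effects on the mediator. The step from mediator to distress is forced to be the same in each arm of the fit, TAU included. A conclusion that anxiety or beliefs mediate the effect of a named therapy then rests partly on how the mediator relates to distress among people who did not receive that therapy.

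Equal slopes are an assumption, and the protocol gives some reason to doubt it. In the earlier trial the predictive value of anxiety reduction depended on sense of voice presence, a rating of the dialogue with the avatar. TAU participants have no such dialogue. The background also argues that some people may need the processes of phase 2 beyond anxiety reduction. At stake are the mechanism conclusions for each form of therapy; the primary efficacy comparison is not affected.

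**Working it through.** **Inputs.** The protocol gives no figure for the mediation analysis. The analysed number per arm comes from its sample size section {14}, which reproduces: n = 2(z₀.₉₈₂₅ + z₀.₉₀)²/d² = 2(2.108 + 1.282)²/0.5² = 91.9, so 92 per arm, and 276/0.8 = 345 recruited. Everything else is assumed: each therapy shifts the mediator by a = 0.5 SD, mediator SD and residual SD are 1, and slopes b are listed as TAU/Brief/Extended. Sizes are absolute values. The true indirect effect of a therapy is evaluated at the slope in its own arm.

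**What the common slope estimates.** With equal arm sizes and equal within-arm mediator variance, the main-effects model estimates the plain average of the arm slopes:

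- planned product = a × (b_TAU + b_Brief + b_Ext)/3
- arm-specific indirect effect for Extended = a × b_Ext

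**Extended versus TAU, one three-arm fit:**

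| Slopes | Planned product | Arm-specific |
|---|---|---|
| 0.3/0.3/0.3 | 0.5 × 0.9/3 = 0.15 | 0.5 × 0.3 = 0.15 |
| 0/0.4/0.4 | 0.5 × 0.8/3 = 0.13 | 0.5 × 0.4 = 0.20 |
| 0/0.2/0.4 | 0.5 × 0.6/3 = 0.10 | 0.5 × 0.4 = 0.20 |
| 0.4/0.4/0 | 0.5 × 0.8/3 = 0.13 | 0.5 × 0 = 0 |
| 0.2/0.2/0 | 0.5 × 0.4/3 = 0.07 | 0.5 × 0 = 0 |

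**How often mediation is declared.** This was simulated with 3,000 trials per setting, requiring both paths to be significant at 5%:

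- 0.4/0.4/0: about 91% with the common slope, about 5% with the slope of Extended alone.
- 0.2/0.2/0: about 54% against 4%.
- 0.3/0.3/0.3: about 92% against 74%. Here the common slope is correct and more powerful.

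**Pairwise fit.** The article does not say whether the three arms are fitted together; naming allocation as a covariate suggests that they are. Fitting Extended and TAU alone does not remove the problem, because TAU still shares the slope. With 0.4/0.4/0 the product is 0.5 × (0.4 + 0)/2 = 0.10 SD against 0, declared in about 69% of trials. With 0/0.4/0.4 it is 0.5 × (0 + 0.4)/2 = 0.10 SD against 0.20.

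**The decomposition.** With the same participants and covariates in both models, the fitted direct effect equals the total effect minus a × b. Adding the product back returns the total exactly, whatever the true slopes. The statement that "The indirect and direct effects sum to the total effect" is therefore arithmetically right for the planned estimator, but for the same reason it cannot reveal unequal slopes.

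**The case against.** The strongest objection concerns the evidence. A reader might infer that the background section shows the slope to differ by arm, and that the plan will therefore credit a therapy with mediation borrowed from other arms. The documents do not support this. The result cited there came from the therapy arm of the previous trial alone, so it contains no comparison of slopes between arms. It used in-session anxiety, with voice frequency and overall severity as outcomes; the planned analysis uses daily-life ESM anxiety or BAVQ-R beliefs, with the distress score as outcome. Taken at face value, a modifier present in both therapy arms and absent in TAU suggests a pattern such as 0/0.4/0.4, which means dilution. False credit needs Brief and Extended to differ, or a stronger slope in TAU, and the document shows neither. The 0.4/0.4/0 case also sits awkwardly with Extended containing phase 1. All of this stands, and it limits the claim to a bias that can run either way.

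A reader might also infer that the sum of direct and indirect effects fails. It does not; only the reading of the parts as arm-specific natural effects is affected.

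Third, a simpler main mediation model is defensible for a secondary analysis, and the common slope is more powerful if it is right. ESM is done only by participants who consent to it, so numbers for the anxiety hypothesis may be smaller: at an assumed 60 per arm and slopes of 0.3, power is about 75% against 48%. This argues for reporting both models, not for replacing one with the other. The unseen analysis plan may already include the interaction, but the article lists the terms without it.

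**Conclusion.** The point holds as a mismatch between a stated model and arm-specific hypotheses. The planned product is the indirect effect of each therapy only if the mediator-outcome slope is the same in every arm of the fit, and the article neither states nor checks that condition. Under the assumptions above, a slope absent in TAU loses about a third of the true effect (0.13 against 0.20 SD). A slope absent in one therapy arm but present elsewhere can give that arm an effect of 0.07 to 0.13 SD that is not its own. With equal slopes there is no bias. The slopes and the mediator effect are assumptions, since the protocol supplies none, so these figures show what could happen and are not a forecast. As a secondary analysis, this merits an inexpensive improvement and does not threaten the main result.

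**What to change.** In the additional analyses section {20b}, add an outcome model with allocation-by-mediator terms. From it, report natural direct and indirect effects for Brief versus TAU and Extended versus TAU, with bootstrap intervals, beside the planned common-slope product. With an interaction in the model the decomposition depends on the arm whose slope is used, so state that the indirect effect is evaluated at the slope of the therapy arm. State also whether the fit is three-arm or pairwise, and that arm-specific mediation conclusions will be qualified where the two models disagree.

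This takes two extra model terms in a three-arm fit, some analysis work and no new data. The downside is precision: if slopes are truly equal, arm-specific intervals are wider, with power of about 74% against 92% at 92 per arm under assumed slopes of 0.3, and lower still for ESM mediators if fewer participants consent. Keeping the common-slope product in the report preserves the more precise estimate for that case. If the full analysis plan already contains this model, one sentence in the protocol settles the point.
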